### Sample size

Power analysis indicated that 129 participants per condition are required in order to detect a difference in symptom reduction, equivalent to a standardized effect size of at least 0.35 in a two-sided test at alpha = 0.05 and a power of (1-beta) = 0.80.

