#### Primary outcome measures

Primary outcome measures include the severity of panic symptoms and PD diagnoses.

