### Analyses

All analyses were conducted in agreement with the intention to treat principle [56], hence all participants were analyzed in the condition to which they were randomized, and missing endpoints at follow-up were imputed using a regression model with the best available predictors of outcome and the best predictors for dropout. The first set of predictors is required to get the most precise estimates for the missing values; the latter to correct for bias that may stem from differential loss-to-follow-up associated with T0 variables [57].

In all analyses on effectiveness, we controlled for the clustering of data caused by the multi-site character of the study. Clustering violates the assumption of independence of observations, and may thus affect standard errors and *P *values. So-called 'robust standard errors' and correct *P *values were obtained using the first-order Taylor series linearization method. All analyses were conducted with Stata 9.0 [58].

For the primary outcome on PDSS-SR, a Gaussian regression model was used to test the hypothesis of superior intervention effects in the experimental arm compared to the waitlist control group. We calculated between-group effect sizes at posttest by subtracting the mean posttest score of each condition and dividing the difference by the pooled standard deviation (Cohen's *d*). In the field of psychological interventions, effect sizes in the range of 0.00 to 0.32 are regarded as small, while effect sizes of 0.33 to 0.55 are moderate, and effect sizes of 0.56 to 1.2 are large [59].

As primary outcome we also compared the proportion of participants manifesting a clinically significant change on the PDSS-SR (responders) across the two groups. Clinically significant change was defined according to the criteria proposed by Jacobson and Truax [60]: a change should move from a dysfunctional distribution to a functional one, and the change should be statistically reliable in the sense that the observed change cannot be put down to measurement error in the PDSS-SR. Because we studied a population with subthreshold and mild PD, we considered scores below one standard deviation of the mean pretest score on the PDSS-SR as falling within the functional range [61]. This binary outcome was then used to obtain the odds ratio (OR) using a logistic regression of the binary outcome on the intervention dummy and the numbers-to-be-treated (NNT) using Gaussian regression.

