The sample can be divided in two groups: people with relatively mild manifestations of MINI-DSM-IV panic disorder and those with subthreshold manifestations not meeting the diagnostic criteria. When we focus on the latter group: people at risk of developing panic disorder, we can look at how many of these persons developed PD meeting the diagnostic criteria of the DSM-IV at T1. When we pay attention to the group with mild PD, we can see how many of these persons became PD-free at T1. For the primary outcome on the MINI-Plus we compared the proportion of success across the two groups. Success was defined as: (a) the participant had no PD at T0 and stayed PD free at T1 or (b) the participant had mild PD at T0 and no PD at T1. This yields a binary outcome where failure is coded 0, and success is coded 1. In a next step, this binary outcome was used to obtain the OR and the NNT.

The demographic and clinical characteristics of responders versus non-responders, and success versus failure, were compared using Student's *t *test for independent groups or Pearson's chi-squared tests when appropriate.

For the secondary outcomes on continuous measurement scales, a Gaussian regression model was used to test the hypothesis of superior intervention effects in the experimental arm compared to the wait-list control group. Furthermore, the between-group effect sizes (Cohen's *d*) were calculated. To test the maintenance of the effects at six-month follow-up we used a paired-samples t test to analyze the difference in mean score of the self-report measures in the experimental group from T0 to T1, T0 to T2 and T1 to T2.

To provide a more comprehensive picture of the effects of the intervention, results for the outcomes will also be presented for completers only (defined as participants who attended at least six sessions).

The following variables will be examined as potential mediators: cognitive aspects of panic disorder, symptoms of agoraphobia, anxiety and mastery. Furthermore, potential moderating variables (e.g., socio-demographic characteristics, panic disorder, agoraphobia, treatment credibility and mastery) will be analyzed.

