The following costs are examined for economic evaluation: costs directly related to health care, indirect health care related costs (out-of-pocket costs, costs of informal care), direct costs outside health care (monetary value of production losses caused by absence and reduced productivity), as measured with the TIC-P. The mean total costs for each of the conditions at baseline and T1 were calculated. Then the pre-post difference in costs were calculated to obtain the increase (or decrease) of costs over time in each of the conditions. First, we observed how many participants presented with a clinically significant change on the PDSS-SR across the two groups. The incremental cost-effectiveness ratio (ICER) was calculated as the incremental costs for a health gain of a clinically significant change over three months. Next, we observed how many people stayed PD free at T1. The ICER was calculated as the incremental costs for a health gain of a PD-free survival over three months. Furthermore, we calculated the incremental cost-utility ratio (ICUR) across the experimental and control condition. The ICUR represents the incremental costs (or savings) per QALY (Quality Adjusted Life Years, assessed with the EQ-5D) gained in the experimental condition relative to the control condition. By calculating ICUR the results can be compared to other health care interventions. In all cases, uncertainty was assessed by means of non-parametric bootstrapping (2,500 times) of the data of the individual respondents.

All tests were conducted using a two-sided significance level at α < 0.05.

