We recognize a number of limitations in this study. First, because of the absence of a placebo control, it is not clear whether nonspecific components of the intervention, such as social cohesion and expectation of gain contribute to the possible early intervention effect. Future research should use placebo controlled designs to overcome this problem. Secondly, the time available to study a change in PD status was only three months. For ethical reasons the control group received the intervention a few weeks after T1. For future research to study a change in PD status an extended period is advised. Thirdly, because of financial limitations we could not raise the sample size, so the change of protocol by including mild PD caused a lack of power to analyze a reduction of incidence of PD according to the MINI-Plus. Fourthly, there is no control condition at six-month follow-up after the course. Therefore, definite conclusions that the possible effects at six-month follow-up may be related to the intervention are not allowed. Finally, the extended follow-up period was only six months following the conclusion of the course, but longer follow-up periods are needed to know how long the possible effects will persist.

Notwithstanding the limitations, the development and research of an early intervention in panic disorder – a severe and persistent mental disorder, associated with a large burden of disease and extensive economic costs – is of the utmost importance.

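### Three T1 comparisons are labelled primary and each is tested at two-sided 0.05, with no ranking and no rule for what makes the trial positive

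*Protocol article*

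**What the plan says.** The section on primary outcome measures names two domains without ranking them: "Primary outcome measures include the severity of panic symptoms and PD diagnoses".

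The Analyses section turns these into three comparisons, each called primary:

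- PDSS-SR mean: "For the primary outcome on PDSS-SR, a Gaussian regression model was used to test the hypothesis of superior intervention effects".
- PDSS-SR responders: "As primary outcome we also compared the proportion of participants manifesting a clinically significant change on the PDSS-SR (responders) across the two groups".
- MINI-Plus status: "For the primary outcome on the MINI-Plus we compared the proportion of success across the two groups". Success here is a composite over the whole sample. It covers participants without PD at T0 who remain free of it at T1, and participants with mild PD at T0 who no longer have it at T1.

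All three are T1 comparisons, because the waitlist group is not followed to T2. The Analyses section ends with one level for everything: "All tests were conducted using a two-sided significance level at α < 0.05".

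The Sample size section rests on a single test of symptom reduction. It says "Power analysis indicated that 129 participants per condition are required" and specifies a "standardized effect size of at least 0.35 in a two-sided test at alpha = 0.05 and a power of (1-beta) = 0.80".

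The article nowhere says which of the three comparisons takes precedence, how many must succeed, or how a mixed result is to be read.

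**The concern.** With three primary comparisons at the full 0.05 and no decision rule, the 5% error rate attaches to each test and not to the overall claim of effectiveness. If one success out of three is enough, the chance of at least one false-positive primary result is well above 5%.

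Mixed results also have no agreed reading. The article does not say whether the trial succeeded if the PDSS-SR means do not differ but the responder proportions do, or if the PDSS-SR is positive and the MINI-Plus composite is not. Readers and authors could settle that differently once the data are known.

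A condensed article may leave detail on multiplicity to an analysis plan. This article does not merely leave it open: it assigns the primary label three times and fixes the level for every test.

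**Working it through.** **Inputs from the article.** Three comparisons labelled primary, two-sided 0.05 for each (Analyses); two primary domains (Primary outcome measures); d = 0.35, alpha 0.05, power 0.80, 129 per arm (Sample size); PDSS-SR intraclass correlation 0.81 (Severity of panic symptoms).

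**Assumption.** The article gives no correlations between the test statistics, so a range is shown.

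**Step 1: the stated sample size.** n per arm = 2(1.960 + 0.842)² / 0.35² = 15.70 / 0.1225 = 128.1, rounded up to 129. The t-test version gives 129.1. Power at 129 per arm: 0.35 × √(129/2) = 2.811, and Φ(2.811 − 1.960) = 0.80. The stated figure is reproduced for one unadjusted test.

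**Step 2: family-wise error, independent tests.**

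- Three tests, either direction: 1 − 0.95³ = 0.143.
- Three tests, only results favouring the course: 1 − 0.975³ = 0.073, against 0.025 for one test.
- Two tests (one per domain), either direction: 1 − 0.95² = 0.0975.

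**Step 3: family-wise error, correlated tests.** Trivariate normal simulation under the global null, 2,000,000 draws, each test two-sided at 0.05. Correlations are listed as mean–responder, mean–MINI, responder–MINI.

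| Correlations | Any of three, either direction | Any of three, favouring the course |
|---|---|---|
| 0.3, 0.3, 0.3 | 13.6% | 6.8% |
| 0.5, 0.3, 0.3 | 13.2% | 6.6% |
| 0.5, 0.5, 0.5 | 12.5% | 6.3% |
| 0.7, 0.5, 0.4 | 12.1% | 6.1% |
| 0.8, 0.5, 0.5 | 11.5% | 5.7% |
| 0.9, 0.7, 0.7 | 9.9% | 5.0% |

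For the two domains only (PDSS-SR mean and MINI-Plus), the two-sided rate is 9.0% at correlation 0.5 and 9.8% at 0.

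**Step 4: which correlations are plausible.** The mean–responder correlation was gauged by simulating the Jacobson–Truax rule. The functional cut was set one standard deviation below the pretest mean, and reliable change at 1.96 × √(2 × (1 − 0.81)) = 1.21 standard deviations. With assumed pre–post correlations of 0.4 to 0.7 and assumed mean improvements of 0 to 0.6 standard deviations, the correlation came out at about 0.3 to 0.6. With assumed MINI-Plus correlations of 0.2 to 0.5, the two-sided rate is then about 12.5 to 14%.

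**Step 5: what an alpha split would cost.**

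- Three ways (0.05/3 = 0.0167, critical value 2.394): power at 129 per arm is Φ(2.811 − 2.394) = 0.66; 171 per arm would be needed for 0.80.
- Two ways (0.025, critical value 2.241): power is Φ(2.811 − 2.241) = 0.72; 156 per arm would be needed.
- Single primary or fixed sequence: power for the PDSS-SR mean stays at 0.80 with 129 per arm.

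**The case against.** The strongest reply is that the article never says any one success suffices. If all three had to succeed, there would be no inflation. The aim and the sample size both point to symptom reduction, the responder analysis re-expresses the same scale, and only two domains are formally listed. This stands in part. The inflation is conditional on an any-one reading, which the text neither states nor excludes. Counting only the two domains lowers the rate to 9 to 10%, still about double the nominal level.

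Three stronger readings are tempting but unsupported.

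- **A 12 to 14% chance of a false success for the course.** That range counts significant results in either direction. The stated hypothesis is superiority, and false superiority is about 6 to 7%.
- **The MINI-Plus primary test is admitted to be underpowered.** Strengths and limitations says that including mild PD "caused a lack of power to analyze a reduction of incidence of PD according to the MINI-Plus". That concerns new cases among people without PD at baseline. The primary MINI-Plus outcome also counts remission of mild PD and covers the whole sample. The article does not state its power, so the concession cannot be carried over.
- **A power figure for incidence settles the matter.** It would need an assumed subthreshold share and rates borrowed from the cited college-student workshop trial. It would also describe a comparison that is not labelled primary, and power has no bearing on false-positive error.

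A last objection is that an unseen analysis plan may contain a hierarchy. That is possible, but the article's blanket level and three primary labels would then conflict with it.

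**Conclusion.** The point holds: three primary labels, one unadjusted level, no decision rule. If success on any one may be claimed, the two-sided family-wise error is 14.3% under independence, about 11.5 to 14% under moderate to high positive correlation, and about 10% at very high correlation. False superiority of the course alone runs at about 6 to 7%, against 2.5% for one test.

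These figures rest on assumed correlations, the global null and the any-one reading. The labels, the common level and the fit of 129 per arm to a single test come directly from the article and do not depend on those assumptions. The primary claim is affected, so this should be settled before results are interpreted.

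**What to change.** Name the T1 PDSS-SR mean difference as the single primary outcome at two-sided 0.05, since the 129 per arm matches that test. Then test PDSS-SR responders and, after that, MINI-Plus success in fixed sequence, each at 0.05 and only if the preceding test is significant. Alternatively, class both as secondary. State that the trial is positive only if the PDSS-SR mean difference is significant.

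Other rules would also close the gap, such as requiring all to succeed, Holm, or a split over the two domains. A Bonferroni split costs power at the present size (0.72 for two tests, 0.66 for three), whereas a single primary does not.

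The cost is more than an edit. Most of the article describes conduct in the past tense, and it already reports one protocol change, the inclusion of mild PD. The ranking must therefore be documented and dated, with a statement of whether outcome data had been seen. Success on responders or the MINI-Plus alone could no longer be presented as a primary success. Sample size and PDSS-SR power are unchanged.

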## Discussion

The purpose of this study is to evaluate the effectiveness of this early intervention based on cognitive behavioural principles on the reduction of panic disorder symptomatology. Furthermore, cost-effectiveness of the intervention is evaluated. We predicted that the experimental condition would show superior effects in reducing panic symptoms, improving quality of life and will be cost-effective despite the additional costs introduced by offering the 'Don't Panic' intervention in the first place. This may be regarded to be an important finding, because, to our knowledge, this is the first study that examines the effectiveness of an early intervention for self-referred adults with subthreshold or mild panic disorder, offered by community mental health centres.

### Strengths and limitations

We changed the original protocol by including people with mild PD (PDSS < 13) and, as a consequence, not excluding participants with PD according to the MINI-Plus. People with mild PD are known to be shy in asking professional help. A low threshold intervention may appear accessible and acceptable for these people. In the Dutch mental health care system people with subthreshold or mild mental disorders are usually offered courses as a first step in a stepped-care model in mental health [62-64]. To strengthen the external validity of the trial we decided to include people with mild PD. Furthermore, the results may be highly generalizable as the intervention is studied in its natural setting and the recruitment strategies of both the study and the community mental health centres that offer the course are very similar. Another strength of this trial is the use of an structured diagnostic interview for DSM-IV and ICD-10 psychiatric disorders (MINI-Plus). This makes it possible to analyze changes in PD status, and for randomization to be stratified by subthreshold PD versus mild PD, and by presence versus absence of co-occurring agoraphobia. The latter was done because it was assumed that agoraphobia is a prognostic relevant factor for treatment response in PD.

We recognize a number of limitations in this study. First, because of the absence of a placebo control, it is not clear whether nonspecific components of the intervention, such as social cohesion and expectation of gain contribute to the possible early intervention effect. Future research should use placebo controlled designs to overcome this problem. Secondly, the time available to study a change in PD status was only three months. For ethical reasons the control group received the intervention a few weeks after T1. For future research to study a change in PD status an extended period is advised. Thirdly, because of financial limitations we could not raise the sample size, so the change of protocol by including mild PD caused a lack of power to analyze a reduction of incidence of PD according to the MINI-Plus. Fourthly, there is no control condition at six-month follow-up after the course. Therefore, definite conclusions that the possible effects at six-month follow-up may be related to the intervention are not allowed. Finally, the extended follow-up period was only six months following the conclusion of the course, but longer follow-up periods are needed to know how long the possible effects will persist.

Notwithstanding the limitations, the development and research of an early intervention in panic disorder – a severe and persistent mental disorder, associated with a large burden of disease and extensive economic costs – is of the utmost importance.
